## Statistical methods

The data will be analyzed using computerized statistical software and all data will be entered into REDCap.

### Primary analysis

Descriptive statistics will be used to report demographic data. Demographic data and outcome measures will be tested visually and statistically (i.e., Shapiro Wilks test). Numeric variables will be summarized by means, standard deviations, and 95% confidence intervals (95% CI). Median and interquartile ranges will be used when normal distribution is not met. Categorical variables will be summarized by frequency and proportion. For group comparison with numerical data, a student’s t-test will be used if data is normally distributed, otherwise, a non-parametric test will be used. For categorical data, a chi-square test will be used for group comparison. An intention-to-treat (ITT) analysis of the primary outcome will be conducted by univariable linear regression, including all patients that do not meet the withdrawal criteria, and will be conducted to minimize bias within results. A sensitivity analysis will test the effects of non-adherence to protocol by conducting a per-protocol analysis and includes only patients who comply with the protocol. For missing data points in an outcome measure, a multiple imputation analysis using predictive covariates (age, sex, smoking, alcohol, UCLA activity, ASA grade) [50–52] will be conducted to deal with nonresponse bias. For comparison, we will carry out a sensitivity analysis excluding all the missing values.

Data will be considered statistically significant if *p* values < 0.0471.

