### Interim analyses

We will carry out two interim analyses after trial completion of 25% and 50% of the planned number of included patients, separately for the two age groups. We will use the O’Brien-Fleming rule [37] for determining appropriate significance levels for each analysis, which is determined by time of hypothesis testing (*n*=3) and the overall significance level of *α*=0.05. Under these assumptions, the significance levels are 0.0006 for the first interim analysis, 0.0151 for the second interim analysis, and 0.0471 for the final analysis. Interim analyses will be carried out for both the primary endpoint (DASH) and for serious complications (iatrogenic nerve injury, deep infection, major adverse cardiac events (MACE), other major adverse events, and death) and will be conducted by one-sided tests to determine if the improvement in DASH is significantly above 25 points, respectively if the complication rate is at least 20% higher.

A Data Monitoring Committee (DMC) has been organized to monitor and evaluate the data from the interim analyses. The DMC consists of five independent members including the patient representative (PR), two orthopedic researchers, an orthopedic surgeon, and a nurse.

In the event of one group having zero complications, the significance level cannot be computed by a cChi-square test, and the DMC will have to assess the data due to a statistical variation.

In the event of a patient sustaining several complications, the most severe complication will follow the patient. The complications are ranked in a hierarchy model describing the severity and are ranked from most severe to least severe: death, MACE, deep infection with debridement, other reasons for hospitalization, and iatrogenic nerve injury.

The interim analyses will be conducted by a biostatistician, blinded to the treatment allocation. Data will then be presented to the DMC, in means and proportions and be accompanied with confidence intervals. The DMC will have access to the data unblinded, and if at least one of those two conditions is fulfilled or a statistical variation has occurred at an interim analysis the DMC will be asked to investigate the results in detail and present their recommendation to continue or stop the trial. In the event of disagreement with a split decision (one or more casts a blank vote), the steering committee will be involved in discussing the stopping of the trial.

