### Randomization

A computerized database software, Research Electronic Data Capture (REDCap)© [38] will be used to generate an irreversible random allocation sequence and perform block randomization with selected block sizes of 2 and 4, which will be stratified on site and age (18–64 and +65). Patients will be assigned to the trial with an allocation of 1:1 to either surgical treatment or non-surgical treatment. The trial worker acquires the allocated treatment from the central coordinator with randomization rights to REDCap. The trial worker then initiates the treatment, either by scheduling the surgery date or applying the chosen non-surgical method.

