### Secondary analysis

In order to validate data, a linear regression analysis will be computed with the DASH score as the dependent variable and treatment modality as the independent variable. Additional regression analysis will be carried out between the early crossover group and the primary treatments. A multivariate regression analysis will be conducted to adjust for potential confounders. Variables adjusted for are: age, sex, smoking, alcohol, UCLA activity, and ASA grade. Furthermore, we will analyze the longitudinal observations by applying a linear mixed-effects regression model, including modality and time as well as a modality-time interaction as fixed effects and a random intercept for each patient. Data will be summarized as coefficients with 95% CIs and variance will be summarized as *r*-squares, adjusted *r*-squares, predicted *r*-squares, and standard errors. Coefficients will be considered statistically significant if *p* values < 0.05.

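### The primary DASH model omits the site stratification factor (and age group if the cohorts are pooled), and a same-form regression is judged at 0.05 instead of 0.0471

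*Protocol article*

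**What the plan says.** The Randomization section describes permuted blocks with 1:1 allocation, "which will be stratified on site and age". The Discussion explains why site was chosen: surgical management can differ between sites.

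Under Primary analysis, "An intention-to-treat (ITT) analysis of the primary outcome will be conducted by univariable linear regression". The same section ends: "Data will be considered statistically significant if *p* values < 0.0471". This agrees with the Interim analyses section, where "the significance levels are 0.0006 for the first interim analysis, 0.0151 for the second interim analysis, and 0.0471 for the final analysis".

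Under Secondary analysis, "a linear regression analysis will be computed with the DASH score as the dependent variable and treatment modality as the independent variable". No time point is named. A multivariable model follows: "Variables adjusted for are: age, sex, smoking, alcohol, UCLA activity, and ASA grade". A longitudinal mixed model has treatment, time, their interaction and a patient intercept. The section closes: "Coefficients will be considered statistically significant if *p* values < 0.05".

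Site appears in none of these models, nor among the listed imputation covariates. The Discussion says the two age cohorts are analysed separately, but the Interim analyses and Sample size sections both allow them to be pooled if recruitment is slow.

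**The concern.** When allocation is balanced within sites, differences between sites no longer contribute to the sampling variation of the treatment difference. A model without site still counts them as residual noise. The reported standard error is then too large, the confidence interval too wide, and the true type I error below the nominal level. The trial takes on the complexity of stratifying by site and then gives up the precision that stratification bought. Under pooling the same holds for age group, which the Background describes as related to DASH.

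The second issue is the threshold. Two regressions of the same form, DASH on treatment, sit in adjacent sections with different significance levels. The second is not restricted to time points other than week 52. A week-52 p value of 0.048 would miss the level in the first section and meet the level in the second.

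**Working it through.** **Inputs.** Sample size section: difference 7.0 and SD 14.91 (SHAFT-Y), difference 10.0 and SD 18.59 (SHAFT-E), alpha 0.05, power 0.8, attrition 15%, totals 163 and 124. Primary analysis section: level 0.0471. Assumed, because the protocol gives no value: site share of DASH variance s = 1, 5 and 10%.

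**Step 1: the plan's own sample size.** Per arm, n = 2 × [SD × (1.960 + 0.842) / difference]². This gives 71.22 (Y) and 54.25 (E). Times 2 and times 1.15 gives 163.8 and 124.8, which truncate to the stated 163 and 124. The trial was therefore sized for an unadjusted two-sided comparison at 0.05.

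**Step 2: power of that comparison at the level applied.** With 15% lost, n per arm is 0.85 × 163 / 2 = 69.3 (Y) and 0.85 × 124 / 2 = 52.7 (E). The standard error is SD × √(2/n) = 2.533 and 3.622, so difference/SE is 2.763 and 2.761. The two-sample t-test has power 78.3% (Y) and 78.1% (E) at 0.05, and 77.6% and 77.3% at 0.0471.

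**Step 3: true level when site is ignored.** The critical value for 0.0471 is z = 1.985. The true variance of the difference is (1 − s) times the variance the model assumes, so the effective critical value is z/√(1 − s) and the true level is 2 × [1 − Φ(z/√(1 − s))].

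**Step 4: power with site in the model.** Replace SD by SD × √(1 − s) at 0.0471, ignoring the degrees of freedom spent on site.

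| s (assumed) | z/√(1 − s) | True level, site ignored | Power with site, Y / E | Gain over 77.6 / 77.3% |
|---|---|---|---|---|
| 1% | 1.995 | 0.046 | 78.0 / 77.7% | about 0.4 points |
| 5% | 2.037 | 0.042 | 79.6 / 79.4% | about 2 points |
| 10% | 2.093 | 0.036 | 81.8 / 81.5% | about 4 points |

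The last column is an upper figure. It compares with textbook power, whereas the unadjusted test in a site-stratified trial already has the smaller true variance. Using the noncentrality from step 4 with the t critical value divided by √(1 − s), unadjusted power becomes 77.7, 78.1 and 78.8% (Y) and 77.4, 77.9 and 78.5% (E). The gap then narrows to about 0.3, 1.5 and 3 points.

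**Step 5: the two thresholds.** Primary analysis and Interim analyses agree on 0.0471. Secondary analysis uses 0.05 for a model with the same outcome scale and the same single predictor. The window in which they disagree is 0.05 − 0.0471 = 0.0029.

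**The case against.** The strongest reply is that an unadjusted comparison is valid, that the trial was sized for one (step 1), and that the section headings show which result is primary. Much of this stands, and it limits how far the point goes.

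- A reader might infer that the univariable model is what takes power below 80%. It is not. Most of the shortfall to about 77% comes from inflating by 1.15 instead of dividing by 0.85, and the rest from moving from 0.05 to 0.0471 (step 2).
- A reader might infer that omitting pre-injury DASH or UCLA activity also makes the test conservative. Allocation is not stratified on either, so the unadjusted test keeps its nominal size and only efficiency is lost. The protocol gives no correlation from which to size that loss.
- Pre-injury DASH is not an ordinary baseline covariate here. According to the Baseline data section, the questionnaire goes out after randomization, so patients who know their allocation recall the score. Adjusting for it could introduce bias.
- Age stratification is handled by the separate analyses unless the cohorts are pooled.
- A reader might infer that the rule choosing a t-test or a non-parametric test by normality leaves the confirmatory test undefined. The rule is general, and the section then assigns linear regression specifically to the primary outcome. The ordinary reading is that the specific statement governs.
- The 0.05 regression is headed as secondary and names no time point, and earlier DASH scores are secondary outcomes. It may not be meant for week 52.

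What remains is that site is absent from every listed model, that age group is absent from the primary model under pooling, and that nothing restricts the 0.05 level to comparisons other than the primary one.

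**Conclusion.** The point holds in this limited form and should be corrected before data are seen. The primary model does not reflect the stratified design. The consequence is a loss of precision, not bias or an inflated error rate: a true level of about 0.046 to 0.036 instead of 0.0471, and a power loss of about 0.4 to 4 points at most, for an assumed site share of 1 to 10%. The direction follows from the design, but the size rests entirely on that assumed share. The threshold conflict is narrow (0.0029) and is an ambiguity of wording. The protocol does not show an intention to judge the primary endpoint at 0.05.

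**What to change.** Name one sole confirmatory analysis in each cohort: linear regression of week-52 DASH on allocated arm, adjusted for site (as a random intercept if there are many small sites), age and UCLA activity, plus age group if the cohorts are pooled, judged at 0.0471 or at the level the protocol sets for the pooling scenario. State that the t-test/non-parametric rule does not apply to this comparison. Delete the treatment-only regression under Secondary analysis, or limit it to time points other than week 52. Keep the unadjusted model as a sensitivity analysis.

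These are wording changes. Site, age and UCLA activity are already recorded and no further patients are needed. Baseline data are described as collected after enrolment, so the text should confirm that UCLA activity is recorded before allocation. Pre-injury DASH should become a covariate only if its collection is moved ahead of allocation, which is a change of procedure and not of wording.

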### Recruitment

Patients admitted to the emergency department (ED) in any of the trial sites will be clinically examined and plain radiographs will be obtained to confirm the diagnosis. If the patient fulfills the eligibility criteria, they will be informed of the trial by staff and receive written information with patient participation information and “Researchers rights in a health science research project.” They will be given time to consider and will be scheduled for an appointment with research staff within 10 days. If written consent is obtained at the consultation, randomization will occur immediately after.

Patients will be provided with transport allowance to cover the costs for consultations at 26 weeks and 52 weeks. They further accept telephone calls if they miss follow-up visits to promote participant retention and complete follow-up.

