### Participant withdrawal

If the patient withdraws the consent, patients will be included in the statistical analysis through multiple imputation, if baseline data is obtained, otherwise imputation is not possible, and the patient will be replaced to meet the calculated sample size.

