### Blinding

The trial will consist of several levels of blinding:The primary outcome will be blinded to everyone involved in the trial, apart from the patients and a central trial worker (non-physician), who will only review the questionnaire for completion in REDCapThe statistical analysis will be conducted by a blinded biostatistician

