### Baseline data

The following baseline data will be collected after enrollment: age, sex, height, weight, arm dominance, American Society of Anesthesiologists (ASA) grade, pre-injury UCLA activity score [37], list of current diagnosis and medication, mechanism of injury, radiological variables (AO/OTA and fracture location), previous surgery to the arm, tobacco and alcohol habits, employment and educational status. DASH and European Quality of Life – 5 dimensions (EQ-5D-5L) questionnaires will be sent by REDCap immediately after randomization to obtain pre-injury scores.

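### The rules for withdrawn patients in the primary ITT analysis are inconsistent, and they allow a randomized patient who leaves on learning the allocation to be excluded and replaced

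*Protocol article*

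**What the plan says.** All references are to the protocol article.

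- **Primary analysis:** the ITT analysis of DASH at 52 weeks is a univariable linear regression, "including all patients that do not meet the withdrawal criteria". Missing outcome values are multiply imputed from age, sex, smoking, alcohol, UCLA activity and ASA grade.
- **Participant withdrawal:** when consent is withdrawn, "patients will be included in the statistical analysis through multiple imputation, if baseline data is obtained". Someone who leaves with no such data on record cannot be imputed under this rule, and a new recruit takes the place.
- **Protocol violation:** patients lost to follow-up, and those who cross over outside the permitted window, stay in the ITT analysis. Withdrawal of consent is not mentioned there.
- **Recruitment:** "If written consent is obtained at the consultation, randomization will occur immediately after".
- **Baseline data:** "The following baseline data will be collected after enrollment". For the DASH and EQ-5D-5L, "questionnaires will be sent by REDCap immediately after randomization to obtain pre-injury scores".
- **Blinding:** "The primary outcome will be blinded to everyone involved in the trial, apart from the patients" and one central trial worker. Under Randomization, treatment is set in motion as soon as the allocation is obtained.

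**The concern.** There are two linked problems. First, two sections give different answers on whether a withdrawn patient belongs to the primary analysis set. An analyst could follow either and claim to be following the protocol.

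Second, the replacement rule works after randomization. In an open comparison of surgery with a brace, some patients may leave because of the arm they drew. Such patients leave early, so they are the ones most likely to have no baseline data, and lack of baseline data is what triggers exclusion and replacement. Exclusion can then depend on allocation, and ITT exists to prevent that. The primary regression has no covariates, so it would not adjust for any resulting imbalance. Replacement restores the number of patients but not the comparability of the arms.

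**Working it through.** **1. The rules applied to four kinds of randomized patient**

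| Patient | Primary analysis | Other section that applies |
|---|---|---|
| Lost to follow-up, consent not withdrawn | In, imputed | In (Protocol violation) |
| Crossover outside the window | In | In (Protocol violation) |
| Withdraws consent at week 20, baseline data held | Out | In, imputed (Participant withdrawal) |
| Withdraws consent just after allocation, no baseline data | Out | Out and replaced (Participant withdrawal) |

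The third row is the inconsistency. The fourth row is the exclusion that does not fit ITT.

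**2. Can the fourth patient occur?** The order of events is consent, randomization at once, the patient learns the arm, and the DASH and EQ-5D-5L are sent. The other baseline items, including the imputation covariates, are placed after enrollment. With randomization following directly on consent, that most naturally means after allocation. No section puts baseline capture before allocation, and none confines replacement to patients not yet randomized. So the case can occur. The gap between consent and randomization is also so short that almost every withdrawal would come after randomization.

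**3. The sample size that replacement is meant to protect.** Inputs from Sample size: differences 7.0 and 10.0, SDs 14.91 and 18.59, α 0.05 (taken as two-sided), power 0.8, attrition 15%. Per arm, n = 2 × [SD × (1.96 + 0.84) / difference]², evaluated with unrounded normal quantiles.

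- SHAFT-Y: 71.2 per arm, 142.4 in total; 142.4 × 1.15 = 163.8, against the stated 163.
- SHAFT-E: 54.25 per arm, 108.5 in total; 108.5 × 1.15 = 124.8, against the stated 124.

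The stated figures reproduce when truncated. They already allow for loss, although after 15% loss 163 × 0.85 = 138.6 and 124 × 0.85 = 105.4, slightly below 142.4 and 108.5.

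**4. Illustrative size of the bias.** Let a share f of one arm leave and be excluded, and let leavers have a mean DASH that differs by g from those who stay. The full arm's mean is the stayers' mean plus f × g, so analysing stayers alone shifts the arm mean by f × g. Recruiting further patients who stay does not change this. If both arms lose patients, the bias is the difference between the two products.

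The documents give neither f nor g. Assumed ranges are f = 2–10% and g = 5–20 points.

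- Patients per arm: SHAFT-Y 163/2 = 81.5, so about 2 to 8 leavers; SHAFT-E 124/2 = 62, so about 1 to 6.
- Smallest shift: 0.02 × 5 = 0.1 points. Largest: 0.10 × 20 = 2.0 points.
- Against 7 points: 0.1/7 = 1% to 2.0/7 = 29%. Against 10 points: 0.1/10 = 1% to 2.0/10 = 20%.

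**The case against.** **The sections can be harmonized.** If the withdrawal criteria in Primary analysis mean only withdrawal without baseline data, the two sections agree. The imputation plan and the retention of protocol violators suggest that this may be the intent, and the full protocol behind the article may define the term. The text shown does not say so, however, and this reading still leaves randomized patients excluded and replaced. It narrows the first problem and leaves the second untouched.

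**Timing.** A reader might infer that every patient who leaves on learning the allocation is dropped. The documents do not support that. Only those without baseline data are dropped, and post-randomization timing is explicit only for the DASH and EQ-5D-5L, neither of which is an imputation covariate. Age must be known earlier because it is a stratification factor, and the timeline figure is not shown. What stands is that such a patient *can* be dropped and replaced.

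**Recalled pre-injury DASH.** A reader might infer that a baseline score recalled with knowledge of the arm contaminates the analysis. It is not a covariate in the primary regression, the imputation list or the adjusted secondary model, so no stated analysis is affected by that route.

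**Replacement and the attrition allowance.** A reader might also say that replacement counts attrition twice. No harm follows: extra recruits do not reduce power, and the allowance is slightly short in any case.

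**Magnitude.** The upper end of the illustration is demanding. Ten per cent of one arm and none of the other is 5% of all patients, which equals the whole attrition that the protocol reports for the reference trial. A gap of 20 points exceeds one SD in both age groups (20/14.91 = 1.3; 20/18.59 = 1.1). Nor would imputation remove the whole shift, because it borrows outcomes from patients who stayed and corrects only what the covariates explain. This objection stands, so the figures are not a forecast and not the expected gain from the fix.

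**Conclusion.** The point holds as an inconsistency in who enters the primary analysis, together with a replacement rule that permits exclusion related to allocation in an analysis called ITT. Both follow from the text and do not depend on any assumed rate. The second rests on reading the replacement rule as applying after randomization, which nothing in the article limits.

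The size of the bias cannot be determined. The range of 0.1–2.0 DASH points assumes that 2–10% of a single arm leave, that all of them lack baseline data, and that they differ by 5–20 points from those who stay. With few such patients, or with similar losses in both arms, the effect would be small. It is still worth correcting, because it fixes the primary analysis set and is best settled before outcomes are seen.

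**What to change.** 1. Define one ITT set: all randomized patients, analysed by allocated arm.
2. Delete the withdrawal exclusion from Primary analysis, so that Participant withdrawal and Primary analysis give the same answer.
3. In Participant withdrawal, restrict replacement to patients not yet randomized.
4. Impute withdrawn patients where consent permits use of their data, and report withdrawals by arm and by timing so that readers can judge any imbalance.
5. At the consent visit, before the allocation is released, record the six imputation covariates (age, sex, smoking, alcohol, UCLA activity, ASA grade), and preferably the pre-injury DASH and EQ-5D-5L. Absence of baseline data should then rarely prevent imputation.

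The cost is revised wording in two sections and one step moved within an existing visit, which becomes slightly longer. Imputation will reduce bias from withdrawals only as far as the covariates explain the outcome.

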### Protocol violation

Lost to follow-upTreatment crossover outside the pre-defined interval for early crossover surgery

Patients that meet any of these criteria will remain in the study and be included in the intention-to-treat analysis but omitted from a per-protocol analysis.

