### Sample size

The two groups (SHAFT-Y and SHAFT-E) require individual sample size calculations. Two standard deviations (SDs) were obtained from the data of the FISH trial [13] and were separated in age groups of 18–64 years and 65 years and above. By the distribution-based approach, one half a SD corresponds to the minimal important change (MIC) [49]. The calculations are powered to detect a MIC of 7 points in the young and 10 points in the elderly group in DASH, respectively. Two independent means sample size calculations were performed. For SHAFT-Y the following data were included: mean difference = 7.0, SD= 14.91, *α*= 0.05, and power= 0.8. For SHAFT-E the following data were included: mean difference= 10.0, SD= 18.59, α= 0.05 and power= 0.8. Based on the preceding assumptions and including an attrition of 15%, the total sample size is estimated to 163 patients for SHAFT-Y and 124 patients for SHAFT-E.

The FISH trial [13] experienced 5% attrition, since more sites are involved in SHAFT the attrition is set to 15%.

The steering committee can decide to pool data from both RCTs (SHAFT-Y, SHAFT-E) if recruitment is prolonged.

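### The one missing-data check named, a complete-case comparison, cannot show whether the week-52 DASH result survives dropout that depends on the score itself

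*Protocol article*

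**What the plan says.** All references are to the protocol article.

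- **Primary analysis** plans "a multiple imputation analysis using predictive covariates (age, sex, smoking, alcohol, UCLA activity, ASA grade") for missing outcome data, and says that it "will be conducted to deal with nonresponse bias". The next sentence adds the check: "For comparison, we will carry out a sensitivity analysis excluding all the missing values".
- **Primary analysis** names one other sensitivity analysis, with a different aim: "A sensitivity analysis will test the effects of non-adherence to protocol by conducting a per-protocol analysis". Under **Protocol violation**, patients lost to follow-up are "included in the intention-to-treat analysis but omitted from a per-protocol analysis".
- **Participant withdrawal** states that after consent is withdrawn, "patients will be included in the statistical analysis through multiple imputation, if baseline data is obtained".
- **Secondary analysis** plans to study the repeated scores by "applying a linear mixed-effects regression model, including modality and time as well as a modality-time interaction as fixed effects", with a random intercept per patient. It is not presented as a check on missing data.
- **Sample size** reports 5% attrition in the Finnish source trial and continues: "since more sites are involved in SHAFT the attrition is set to 15" per cent.

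**The concern.** A missing-data sensitivity analysis is useful when it relaxes the assumption behind the main analysis. Here the main assumption is that, given the covariates, patients with a missing score resemble those observed (missing at random). The complete-case regression on treatment alone assumes that missingness is unrelated to outcome within each arm. If the imputation model includes treatment arm, that is at least as strong an assumption. When patients with poor (or very good) results stop answering for reasons the covariates do not capture, both analyses err in the same direction and can agree while both are biased.

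The other planned analyses do not fill the gap. The per-protocol set also drops patients lost to follow-up, and the mixed model is itself valid only under missing at random.

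At stake is whether a positive or negative primary result can be shown to survive informative nonresponse. The outcome is self-reported by patients who know their treatment, and withdrawals are imputed too, so outcome-related withdrawal would feed into the primary estimate.

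**Working it through.** **Inputs** (Sample size, Interim analyses, Primary analysis): target 7 points and SD 14.91 for SHAFT-Y; target 10 points and SD 18.59 for SHAFT-E; total N 163 and 124; 1:1 allocation; planned attrition 15%, source trial 5%; final significance level 0.0471, taken here as two-sided (critical value 1.985).

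**The plan's own figures.** Total = 4 × (1.96 + 0.8416)² × SD² / difference² gives 142.4 and 108.5 before rounding. Multiplied by 1.15, these are 163.8 and 124.8, which matches 163 and 124 rounded down. The inputs are therefore read as intended.

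**Significance threshold at 15% missing.** Evaluable patients are 163 × 0.85 = 138.55 and 124 × 0.85 = 105.4. SE = SD × √(4/N):

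- SHAFT-Y: 14.91 × √(4/138.55) = 2.53; threshold 1.985 × 2.53 = 5.03 points.
- SHAFT-E: 18.59 × √(4/105.4) = 3.62; threshold 1.985 × 3.62 = 7.19 points.

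**Effect of informative dropout.** Let f be the fraction missing in an arm and δ the amount by which its missing patients are worse than imputed. The surgical benefit falls by f(surgical) × δ(surgical) − f(non-surgical) × δ(non-surgical).

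| One-arm shift | SHAFT-Y | SHAFT-E |
|---|---|---|
| 1 SD, 15% missing | 0.15 × 14.91 = 2.2 (32% of target) | 0.15 × 18.59 = 2.8 (28% of target) |
| 1 SD, 5% missing | 0.05 × 14.91 = 0.7 | 0.05 × 18.59 = 0.9 |
| Shift that ends significance, observed effect = target, 15% | (7 − 5.03)/0.15 = 13 (0.9 SD) | (10 − 7.19)/0.15 = 19 (1.0 SD) |
| The same at 5% | (7 − 5.03)/0.05 = 39 | (10 − 7.19)/0.05 = 56 |

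The last row keeps the 15% threshold. With more patients observed the threshold would be lower, so those two shifts are if anything understated.

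A smaller observed effect tips sooner. At an illustrative 6 points in SHAFT-Y the shift is (6 − 5.03)/0.15 = 6.5 points; at 8.5 points in SHAFT-E it is (8.5 − 7.19)/0.15 = 8.7 points. Both are below the respective MIC of 7 and 10. Equal shifts with equal missingness give zero change. With 20% missing in the surgical arm and 10% in the other, a common shift of two MICs moves the result by 0.10 × 14 = 1.4 or 0.10 × 20 = 2.0 points.

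**Would the planned check notice?** A simulation compared complete-case analysis with imputation. Assumptions, none of them from the documents except the 15%: 15% missing per arm; covariates explaining 10 to 20% of DASH variance; in the surgical arm only, log-odds of being missing rising by 1.0 to 1.5 per SD of worse DASH. The first three rows have arm in the imputation model.

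| | SHAFT-Y (true −7) | SHAFT-E (true −10) |
|---|---|---|
| Complete-case mean, informative dropout | −8.8 to −9.6 | −12.2 to −13.3 |
| Imputation mean, informative dropout | −8.7 to −9.2 | −11.9 to −12.9 |
| Average gap between the two: informative / non-informative | 0.4–0.6 / about 0.4 | 0.6–0.8 / about 0.6 |
| Imputation without arm, non-informative dropout | −6.0 | −8.5 |

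Both analyses miss the truth by roughly 2 to 3 points, yet the gap between them is nearly the same as when dropout is harmless. The last row matters for the objection: without arm in the imputation model, a gap appears even when dropout is non-informative.

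**The case against.** The strongest reply is that the text contains no error. Imputation with a complete-case comparison is a common plan, the comparison is not said to test informative dropout, and an analysis plan that is not shown could add such a test. It stands that nothing here is false or self-contradictory, and that the missing analysis should not be counted as a gap in the trial's full documentation. What remains is that the article itself labels this comparison a sensitivity analysis, right after an imputation justified by nonresponse bias, and the comparison does not probe that bias.

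A reader might go further and infer that complete-case always rests on the stronger assumption, or is worthless. The documents do not support that. The listed covariates do not name treatment arm. If arm really is left out, the two assumptions are not nested, the imputation pulls the effect toward zero, and the comparison could expose that fault. It therefore has some value against a misspecified imputation model.

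The mixed model also deserves credit. It uses the 6-, 12- and 26-week scores, so patients who do visibly badly before they stop answering are partly accounted for. It is still a missing-at-random analysis.

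Finally, the one-arm shift is a stress case, and at 5% attrition the tipping shifts are implausibly large. Transport allowance, telephone calls after missed visits and assisted questionnaire completion may keep missingness low. All of this limits the size of the point; none of it tests the assumption.

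**Conclusion.** The point holds as a modest improvement. The one missing-data sensitivity analysis named does not allow missingness to depend on the unobserved DASH score, and neither do the imputation and the mixed model. Provided arm is in the imputation model, agreement between complete-case and imputed results is not evidence against informative dropout.

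The size depends on attrition and on how one-sided the departure is. At 15% missing, a target-sized effect withstands one-arm departures of up to about 0.9 to 1.0 SD; a smaller but significant effect may not withstand one MIC. At 5% missing, a target-sized effect is robust to any plausible departure. These figures rest on the planning SDs, a normal approximation, and an SE computed from evaluable patients and held fixed as scores are shifted.

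It should not be read as showing that the primary result will be biased or that the planned imputation is wrong. The documents give no evidence about the actual dropout mechanism.

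**What to change.** In Primary analysis, keep the complete-case result as a descriptive comparison. Define the missing-data sensitivity analysis as a delta-adjusted version of the planned imputation:

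- State that treatment arm is in the imputation model.
- Add a fixed shift to the imputed week-52 DASH scores, separately in each arm and in both directions, for example from −20 to +20 points. Both directions are needed because very good as well as poor results can lead patients to stop answering. This range covers the tipping shifts of 13 and 19 points.
- State whether shifted scores are held within the 0 to 100 scale.
- Report, for SHAFT-Y and SHAFT-E, the shift or pair of shifts at which the conclusion at 0.0471 changes, beside the missingness observed in each arm.

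This needs no new data and only a few lines of code on imputed data sets already planned. The downside is one more table, and the conclusion may look less robust. It should be fixed before outcome data are seen.
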